**Methods/Design:**

**Endoscopic Saphenous harvesting with an Open CO_2 _System **trial includes two parallel vein harvesting arms in coronary artery bypass grafting surgery. It is an interventional, single centre, prospective, randomized, safety/efficacy, cost/effectiveness study, in adult patients with elective planned and first isolated coronary artery disease. A simple size of 100 patients for each arm will be required to achieve 80% statistical power, with a significant level of 0.05, for detecting most of the formulated hypotheses. A six-weeks leg wound complications rate was assumed to be 20% in the conventional arm and less of 4% in the endoscopic arm. Previously quoted studies suggest a first-year vein-graft failure rate of about 20% with an annual occlusion rate of 1% to 2% in the first six years, with practically no difference between the endoscopic and conventional approaches. Similarly, the results on event-free survival rates for the two arms have barely a 2-3% gap. Assuming a 10% drop-out rate and a 5% cross-over rate, the goal is to enrol 230 patients from a single Italian cardiac surgery centre.

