**Discussion:**

The goal of this prospective randomized trial is to compare and to test improvement in wound healing, quality of life, safety/efficacy, cost-effectiveness, short and long-term outcomes and vein-graft patency after endoscopic open CO_2 _harvesting system versus conventional vein harvesting.

The expected results are of high clinical relevance and will show the safety/efficacy or non-inferiority of one treatment approach in terms of vein harvesting for coronary artery bypass grafting surgery.

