### Primary end points

We have two primary end points (see Appendix 1) with different deadlines:

• a short-term one (6 weeks after CABG surgery), regarding freedom from wound complications, defined as cellulitis, edema, ecchymosis, hematoma, cellulites, drainage, necrosis, dehiscence, debridement; leg wound infection according to ASEPSIS score;

• a long-term one (2 years after CABG surgery), regarding freedom from MACE, i.e. death, myocardial infarction, recurrent angina or congestive heart failure due to vein graft failure with assessment of vein-graft patency.

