### Secondary end points

The secondary end points (see Table 1) include for both arms:

**Table 1 T1:** Study design

Inclusion Criteria:	Exclusion Criteria:
Elective planned CABG surgery	Emergency revascularization: patients with hemodynamic instability or requiring inotropic or intra-aortic balloon support

First isolated CABG surgery	Previous cardiac surgery

Adult patients (18 years and older) and competent to give informed consent	Planned concomitant valve surgery

	Bad varicous veins

	Previous safenectomy

	History of deep vein thrombosis

	History of suffered trauma on the lower extremity

	Preoperative legs immobilization

	Previous leg wound complications

	Coexisting illness with life expectancy < five years

• identification of predictors for a possible development of a harvest-site complication: preoperative demographics such as sex, obesity, diabetes, peripheral vascular disease and operative demographics such as EVH vs. CVH approach, number of bypass grafts, time on bypass, harvest site (below or above the knee), characteristics of the bandage will be considered and analyzed;

• evaluation of differences between EVH and CVH in operative time, mobility time, number of medications, hospital length of stay, readmission for leg wound complications or need for outpatient wound management resources and generally in all resources that need to be allocated;

• Evaluation of differences between EVH and CVH in the quality of the harvested venous conduits;

• Comparison of health-related quality of life (EUROQol-5D) and leg pain score and identification of factors, in addition to treatment allocation, that are associated with variations in quality of life outcomes.

• correlation of the long-term outcome with the vein histological scores determined at harvest time.

For the EVH arm only:

• effect of the harvest site, whether below or above the knee;

• effect of the vein preparation solution;

• effect of an uncontrolled distension pressure or no touch technique on vein patency and long-term outcomes;

• assessment of systemic carbon dioxide absorption.

ESOS is meant to be an interventional, single centre, prospective randomized study with an all-comers design. Each cohort will initially be formed by 115 patients. This number has been selected to balance statistical requirements and resource limitations.

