A few considerations on the selected sample size are opportune. Assuming the values conventionally accepted for the drop-out and cross-over rates of ≤ 10% and ≤ 5% of the patients, follow-up will see two cohorts of approximately 100 patients for each. This means that data computed as percentage within each cohort should be correctly reported with an uncertainty of ± 5%.

It is well known that the power of the statistical test used to carry out comparisons between two sets of data depends both on the sample sizes and the entity of the difference between data observed in the two groups. A tiny difference has difficulty to be evidenced as statistical significant even with a very large sample size, while a substantial difference can be easily assessed as significant even with a small sample size.

In a trial in which the analysis wants to take into account several outcomes, the presence of a wide range of observable differences makes very difficult a "valid-for-all" estimate of the sample size necessary to achieve the desired test power (usually 80%) or inversely on the test power predicted on the base of the actual sample size.

In our trial, as far as the short-term outcome is concerned, previous studies [8,9] suggest a six-week leg wound complication rate of about 20% in the CVH arm and less than 4% in the EVH arm. With this risk/prevalence difference of 16%, and the predicted sample size of 100, the power based on normal approximation is about 94% (91% if we apply the continuity correction), and thus very good: a power of about 80% would be reached already with a sample size around 80.

The situation changes dramatically when we consider the mid- and long term outcomes. Previously quoted studies [2] suggest a first-year vein-graft failure rate of about 20% with an annual occlusion rate of 1% to 2% in the first six years, with practically no difference between the EVH and CVH approaches. On the basis of previous comparative trials of EVH versus OVH, none of the clinically relevant cardiovascular outcomes differed significantly for EVH compared with OVH (Allen et al. [11] reported survival free of MACE at up to 5 years as 75% vs. 74%, p = 0.85). A 2-3% of non-inferiority margin is therefore planned in this protocol study. The 80% test power goal, with such small risk prevalence difference requires sample sizes of at lest 3000 for each cohort, values well beyond any practical implementation in a single medical centre, at least in a lifetime.

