On the basis of these considerations, the initial recruitment number of 115 patients per cohort, with end-point number of about 100 patients, sustainable from the point of view of human and financial resources, looks fully acceptable.

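### The 2-3% non-inferiority margin for long-term outcomes, including the 2-year MACE primary end point, is incompatible with about 100 patients per arm

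*Protocol article*

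**What the plan says.** The section on primary end points names two. One is freedom from wound complications at 6 weeks. The other is "a long-term one (2 years after CABG surgery), regarding freedom from MACE".

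Under Trial Population, and Statistical Analysis, the sample size discussion finds ample power for the wound end point. It then turns to the mid- and long-term outcomes, cites earlier comparisons that found almost no difference between the two techniques, and states: "A 2-3% of non-inferiority margin is therefore planned in this protocol study". The next sentence says that 80% power for so small a difference "requires sample sizes of at lest 3000 for each cohort, values well beyond any practical implementation in a single medical centre". The discussion closes by finding that "the initial recruitment number of 115 patients per cohort, with end-point number of about 100 patients" is acceptable; the full judgement reads "with end-point number of about 100 patients, sustainable from the point of view of human and financial resources, looks fully acceptable".

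The abstract carries two related statements. Its Methods/Design paragraph says "A simple size of 100 patients for each arm will be required to achieve 80% statistical power", and limits this to the majority of the hypotheses. Its Discussion paragraph says that the expected results "will show the safety/efficacy or non-inferiority of one treatment approach in terms of vein harvesting".

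For event-free survival the article names Kaplan-Meier estimates and the log-rank test of difference. If p exceeds 0.05, a power estimate follows.

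**The concern.** A non-inferiority margin is a commitment: the trial succeeds on that end point if the confidence limit for the excess risk stays below the margin. Here the margin is attached to outcomes that include a primary end point. By the protocol's own figure the planned size is about one thirtieth of what is needed (100 against 3000), yet the size is accepted and a non-inferiority result is announced. The margin is also given as a range, so there is no single limit to test against.

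What is at stake is the reading of the 2-year result. The main Discussion links a definite recommendation of endoscopic harvesting to long-term event-free survival. If the log-rank test is not significant, which is likely at this size under a small true difference, a margin and a non-inferiority statement already in print invite the conclusion that the techniques are equivalent. The data could at the same time be compatible with an excess MACE risk of around 10 points.

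**Working it through.** **Inputs from the protocol article**
- Margin m: 2 to 3 percentage points (Trial Population, and Statistical Analysis).
- Evaluable patients per arm n: about 100, from 115 recruited. Allocation is equal: "Each cohort will initially be formed by 115 patients" (Secondary end points).
- Significance level 0.05 and power goal 80% (abstract).
- MACE-free rates quoted from earlier studies: 75% vs 74% at 5 years and 80% vs 83% at 3 years, that is event risks of 17-26%.

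**Assumptions, because the article does not give them**
- True 2-year MACE risk p, equal in both arms: 10-25%, with 5% as a sensitivity case.
- One-sided level 0.025 for non-inferiority, with 0.05 as a sensitivity case.

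**Step 1: the plan's own figures reproduce.**
- Wound complications, 20% vs 4%, 100 per arm, two-sided 0.05: power 94.2%, or 91.1% with continuity correction. The article says 94% and 91%.
- At least 3000 per cohort: a two-sided comparison of 20% vs 23% needs 2943 per arm (3009 with continuity correction). A non-inferiority design needs n = (1.96 + 0.842)² × 2p(1−p)/m². With p = 0.25 and m = 0.03 this is 7.85 × 0.375/0.0009 ≈ 3271; with p = 0.20 it is 2791. So 3000 is a fair lower bound, at the 3% end of the margin. At m = 0.02 the same formula gives 6280 (p = 0.20) to 7359 (p = 0.25).

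**Step 2: non-inferiority power at 100 per arm.**

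Power = Φ( m / SE − 1.96 ), with SE = √(2p(1−p)/100).

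| True risk p | SE | Power, m = 2% | Power, m = 3% | 95% CI half-width (1.96 × SE) |
|---|---|---|---|---|
| 5% | 0.0308 | 9.5% | 16.2% | 6.0 points |
| 10% | 0.0424 | 6.8% | 10.5% | 8.3 points |
| 17% | 0.0531 | 5.7% | 8.2% | 10.4 points |
| 20% | 0.0566 | 5.4% | 7.6% | 11.1 points |
| 25% | 0.0612 | 5.1% | 7.1% | 12.0 points |

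Example for p = 0.25, m = 0.03: 0.03/0.0612 − 1.96 = −1.47, and Φ(−1.47) = 0.071. Simulating the confidence limit over risks of 10-25% gives 5.3-10.9%, in agreement.

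**Step 3: sensitivity.**
- One-sided 0.05, risks 10-25%: 9.4-17.4%.
- All 115 per arm evaluable, one-sided 0.025: 5.4-11.5%.
- True rates equal to the quoted 75% vs 74% MACE-free, which favours endoscopic harvesting: 7.0% (m = 2%) to 9.5% (m = 3%).
- A large true benefit, MACE 15% vs 25% in favour of endoscopic harvesting: SE = √((0.15×0.85 + 0.25×0.75)/100) = 0.0561. Power is Φ(0.12/0.0561 − 1.96) = 57% at m = 2% and Φ(0.13/0.0561 − 1.96) = 64% at m = 3%.

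**Step 4: the stated analysis.** A log-rank test asks whether the curves differ. Non-significance bounds nothing; non-inferiority needs a confidence limit compared with the margin. A power estimate after p > 0.05 does not supply that limit.

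**The case against.** The strongest reply is that the authors hide nothing. They say plainly that the picture changes for long-term outcomes and that a single centre cannot reach the numbers needed. They justify 115 per arm by resources and by the wound end point, for which power is good. An analysis plan that is not shown may also specify a non-inferiority test. All of this is fair. It does not remove the problem: having disclosed the shortfall, the plan still sets the margin, accepts the size and announces non-inferiority, and no analysis plan can add the missing precision.

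Some stronger readings are tempting, but the documents do not support them:
- A reader might infer that 80% power is promised for MACE. The abstract limits that statement to the majority of hypotheses, and the sample size text excludes the long-term outcomes.
- A reader might infer that the end point cannot succeed whatever the true effect. It can: a true 10-point benefit gives 57-64% power. The authors do hope for a benefit, although the sample size text plans on practically no difference.
- A reader might infer that the 3000 is miscalculated. It holds as a lower bound.
- A reader might infer that the margin was taken from the 80% vs 83% comparison. The sentence that introduces the margin rests on the 75% vs 74% trial.
- The announced conclusion is worded as an alternative and does not name MACE. Still, the only non-inferiority margin in the article is the one for long-term outcomes, so a reader will connect the two.

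It also stands that the 10-25% risk range is assumed. The end-point wording can be read as limiting events to those due to graft failure, and lower risks are then plausible. At 5% power rises to about 10-16%, which is still far from 80%.

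**Conclusion.** The point holds in this form. A 2-3% non-inferiority margin for outcomes that include a primary end point cannot be reconciled with about 100 patients per arm, by the protocol's own figure of at least 3000. With equal true 2-year risks of 10-25% and one-sided 0.025, power is about 5-11%; at a 5% risk it is about 10-16%. Over the 10-25% range the confidence interval half-width is 8-12 points, roughly three to six times the margin (8.3/3 ≈ 2.8 to 12.0/2 = 6.0). The exact figures depend on the assumed event rate and level. The conclusion does not change over the ranges shown: non-inferiority is very unlikely to be demonstrated unless endoscopic harvesting is substantially better. The defect is an internal contradiction that affects how a primary result will be read, so it should be corrected.

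**What to change.** 1. Delete the 2-3% margin and the non-inferiority claim for long-term outcomes, both in the sample size text and in the abstract.
2. Report 2-year MACE and vein-graft patency as risk differences with 95% confidence intervals. State that a non-significant log-rank test is not evidence of equivalence or non-inferiority.
3. Restrict the abstract's power statement to the 6-week wound end point: about 94% (91% with continuity correction) at 100 per arm for 20% vs 4%.
4. Say that the long-term comparison is for estimation only. Give its expected precision with the event-rate assumption beside it, for example a half-width of 8-12 points if the 2-year risk is 10-25%.

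MACE need not lose its primary status to resolve the contradiction. If the sponsor chooses to change that status, recruitment has already begun and the trial is registered, so a documented amendment and a registry update are needed.

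Cost: no extra patients and no new data. The sponsor gives up a non-inferiority claim that the trial could hardly have supported.

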### Procedural techniques

The leg wound protocol established for the trial calls for all patients, irrespective of the cohort to which they have been allocated, to receive 1 g cefazolin and 1 g vancomycin hydrochloride (Vancocin) preoperatively. They will also receive a povidoneiodine (Betadine) scrub and preparatory solutions before skin incision.

Antibiotic therapy will be continued for an additional 48 hours post-operatively. All wounds will be closed at the time of heparin reversal and the administration of protamine.

### Conventional harvesting

Conventional vein harvesting will be performed through longitudinal incisions over the course of the saphenous vein (SV), starting at the medial malleolus. The length of the incision will depend on the amount of vein required (at least a minimum of 18-20 cm per each vein segment). The incisions will be closed in layers, with absorbable subcutaneous and subcuticular sutures. Elastic bandage wrapping or support stockings will be used in all patients, until up to at least 72 hours after harvesting. 

### Endoscopic vein harvesting

A 2,5 cm longitudinal incision will be made in the thigh above the knee (two finger-breadths posterior to the medial edge of the tibia). After initial identification of the saphenous vein, a plane of dissection along the anterior surface of the vein will be performed using as endoscopic dissector the Sorin ClearGlide, an open CO2 EVH system. This device is not dependent on gas insufflation to maintain tissue separation and/or the tunnel. The insufflator of the endoscopic-tower is capable to regulate the gas flow and maintain a zero gradient pressure in the cavity. A low flow of CO_2 _is required (4 l/min) to flush the working channel and optimize the vein exposure.

Vein harvesting will be initially directed proximally until 2 cm below and lateral to the pubic tubercle, where the SV enters the cribriform fascia (*fascia lata*) to join the femoral vein. Then, depending on the amount of vein required, distal (below the knee) harvesting may be extended until the medial malleolus. Branches will be divided using an electrothermal bipolar tissue-sealing cautery (Ligasure™ 5 mm Laparoscopic Instrument Valleylab). SV will be divided distally to initial incision using endoclips (Endosurgery) and endoforceps (SorinGroup), and a small stab incision will be made to pull the vein.

The incision will be closed with absorbable subcutaneous and subcuticular sutures, starting after reversal of the heparin infusion. Elastic bandage wrapping or support stockings will be used in all patients, up to at least 72 hours after harvesting.

After harvesting, the vein will be cannulated and prepared with papaverine and heparinised blood, and branches will be ligated using titanium clips or/and 3-0 silk ties.

### Histology

A first check on the validity of the endoscopic device (given for granted the surgeon's ability) may be furnished by the histological evaluation of specimens collected during the harvest, with the assessment of the level of disruption in the various layers of the venous wall. Absence, or minimal presence of disruption should constitute a good start for a satisfactory vein outcome.

The uniformity, continuity, and integrity of vein structures will be assessed by histological studies conducted in a blind fashion by two of the authors ([name] and [name]), who will evaluate the vein histological structures according to the so-called "Griffith score" [21] which estimates the percent disruption of each histological structure (see Table 2).

**Table 2 T2:** Histology Grading

The histological structures to be evaluated are the:	**The numeric grading system estimates the percent disruption of each histological structure and will be scored according to the following scale **[2]:	
*endothelial layer*	0	Intact or not disruption

*elastic lamina*	1	< 10%

*medial smooth muscle and connective tissue*	2	10-25%

*adventitial connective tissue*.	3	25-50%

	4	> 50%

At this purpose it is important to point out that the results obtained on the specimens collected during the learning curve are very encouraging: the average overall score is 0.3 ± 0.6 over a total of 4.0, with a flat "zero" (intact structure) for the medial connective tissues, medial smooth muscles and adventitial connective tissues.

Another open issue is whether the vein preparation procedure might influence SV histology. As now, there is no standard vein-preparation solution used in clinical practice [22,23]. The authors will investigate whether the preparation solution and a controlled distension pressure or no touch technique might prevent histological disruption and influence vein patency and long-term outcomes. (Appendix 1)

## Discussion

Nowadays, a research to evidence benefits, harms and resource implications of EVH vs. OVH must not only meet the requirements of being prospective, randomized and including a great number of baseline, inter-operative, post-operative and follow-up co-founding variables, but needs also to exploit the latest improvements in the available technologies of vein harvesting.

The Endoscopic Saphenous harvesting with an Open CO_2 _System (ESOS) Trial, was configured after these guidelines.

Its primary goal is to compare and to quantify improvements in short and mid-term outcomes after endoscopic open CO_2 _harvesting (EVH) versus conventional open vein harvesting (CVH): safety/efficacy, leg wound infections and morbidity, patient satisfaction, short and long-term outcome, with histological and angiographic studies will be matter of thorough investigation.

The results on wound healing, mobility, patient satisfaction, health-related quality of life, safety/efficacy, cost-effectiveness are expected to be available shortly after the beginning of the trial. The mid-term outcomes and vein-graft patency will be estimated at the end of the 2-year follow-up, when a possible extension of the period of observation will also be considered.

A secondary goal of ESOS is to provide guidance to physicians on optimal CABG strategies for patients with different risk levels. A more widely spread and accurate knowledge on this issue may also help patients in their choices in a difficult predicament of their life when they have to take fundamental decisions for their health.

When compared to CVH procedure, EVH is expected to confer a 16% reduction in leg wound infections. If the use of new improved instrumentation will also improve the long-term event-free survival rate, as we hope, endoscopic saphenous vein harvesting should then be definitely recommended to patients with CAD, also for the high level of satisfaction usually reported by patients undergoing this minimally invasive procedure.

This study, besides providing new information aimed to improve the quality of care for CAD patients, will also assess the cost/effectiveness of this approach as far as in-patient and out-patient care is concerned.

### Trial status

Currently including patients

## List of abbreviations used

ESOS: Endoscopic saphenous harvesting with an open CO_2 _system; CABG: Coronary artery bypass grafting; CAD: Coronary artery disease; PCI: Percutaneous coronary intervention; EVH: Endoscopic vein with open CO_2 _harvesting; CVH: Conventional vein harvesting; SV: Saphenous vein; MACE: Major adverse cardiovascular events: death; myocardial infarction; revascularization (PCI or CABG) for ischemia or angina recurrence; GF: vein-graft failure at least 75% of stenosis at angiographic study; GO: vein-graft occlusion
